### 1. Definition of BPD variable

**Original definition:** BPD – this morbidity is evaluated at 36 weeks PMA and will be analysed including the complete ITT population with deaths considered as non-events but their follow-up time will contribute to the total follow-up in the analyses of event rate performed by Poisson regression. Sensitivity analysis of BPD will be performed handling all deaths as endpoint also beside confirmed BPD. Drop-out due to other reasons will be considered as non-event.

**Clarification:** BPD – this morbidity is evaluated at 36 weeks PMA, defined as need for supplemental oxygen that time point, and will be analysed including the complete ITT population with deaths considered as non-events but their follow-up time will contribute to the total follow-up in the analyses of event rate performed by Poisson regression. Sensitivity analysis of BPD will be performed handling all deaths as endpoint also beside confirmed BPD. Drop-out due to other reasons will be considered as non-event.

### 2. Clarification on the sensitivity analysis of severe ROP and NEC

**Original definition:** The sensitivity analysis will be performed on ITT population comparing cumulative incidence rates adjusted for death as competing risk, other drop-outs handled as censored in the survival analysis. Gray's test will be performed for this purpose. Moreover, the effect of the sensitivity analysis will be explained by Hazard Ratios (HR) with 95% CI obtained from Cox proportional hazards models.

**Updated definition:** The sensitivity analysis will be performed on ITT population comparing cumulative incidence rates adjusted for death as competing risk, other drop-outs handled as censored in the survival analysis. Gray's test will be performed for this purpose. Moreover, the effect of the sensitivity analysis will be explained by sub-distribution Hazard Ratios (HR) with 95% CI obtained using Fine and Gray method (in order to correspond to the competing risk analysis).

### 3. Clarification on the analysis of growth data secondary variable

**Original definition:** Postnatal growth development of weight, length, head circumference, at day 0, day 7, day 14, postnatal age (PNA) week 3-7, PMA week 30-40. For infants born at GA $\geq$ 24 weeks SDS will be calculated and summarized per treatment group. Otherwise, for all infants individual

|                                     |  |                                    |             |
|-------------------------------------|--|------------------------------------|-------------|
| STATISTISKA KONSULTGRUPPEN          |  | Note-to-SAP 1                      |             |
| Protocol:
Mega Donna Mega |  | Protocol No:
MEGADONNAMEGA 16-7 |             |
|                                     |  | Version:
1.0                    | Page 2 of 2 |

growth curves will be created separately by sex and GA week for the two treatment groups. No imputation of missing data is planned.

**Updated definition:** Postnatal growth development of weight, length, head circumference, at day 0, and PMA week 30-40, will be analysed using mixed models for repeated measures (MMRM). SDS will be calculated and summarized per treatment group using Niklasson and Albertsson-Wikland 2008 reference. At birth, this reference will be extrapolated and used also for infants born at GA <24 weeks. No imputation of missing data is planned.

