##### **A. Conventional parenteral fatty acid treatment with Clinoleic**

##### **B. Enteral supplement of AA (100mg/kg/day) and DHA (50 mg/kg/day) from birth to 40 weeks postmenstrual age in addition to conventional parenteral fatty acid treatment with Clinoleic.**

Enteral supplementation with AA:DHA will start at second enteral feeding after birth and continue once daily to postmenstrual week 40 + 0. The supplementation will be delivered prior to feeding (0.1-1ml, according to dosing scheme, Appendix A). If the infant does not tolerate any enteral feeding, the supplement will be given as long as gastric retention is administered.

The intervention group will receive a daily dose of 100 mg AA/kg/day and 50 mg DHA/kg/day (Formulaid™ 2:1 DSM). Dose adjustment will be performed after the infant has regained its birthweight and weight gain results in an increase of 0.1 ml or more (see Appendix A).

Formulaid™ is produced from a blend of algal, fungal, and high oleic sunflower oils, and contains AA and DHA (triglyceride form) in a ratio of 2:1. Approximate concentrations are 265 mg/g and 135 mg/g. The study oil will be dispensed 1ml purple syringes long time stored at -80 C. Syringes are then provided to the neonatal ward where they can be stored for up to three months in +4 - +8 °C. .

As we will have clinical record forms (CRF's) online the randomization is given in the CRF when the patient's parents have agreed to participate in the study.

Randomization will be as follows; GA  $\leq$  24 weeks +6 days, n= 84, GA 25 weeks +0 days to  $\leq$  26 weeks +6 days, n= 84 and GA 27 weeks +0 days to  $\leq$  27 weeks +6 days,

n=42 (in order to receive equal number of infants with conventional treatment and infants treated with AA:DHA supplementation in relation to morbidity outcome. In order to adjust for center variability each center (n=3) will recruit as follows; GA  $\leq$  24 weeks +6 days, n= 14 (conventional) +14 (treated), GA 25 weeks+0 days to  $\leq$  26 weeks +6 days, n= 14 (conventional) +14 (treated) and GA 27 weeks +0 days to  $\leq$  27 weeks +6 days, n=7 (conventional) +7 (treated).

The treating nurse/doctor will receive the randomization on-line. The examiners (ophthalmologists, radiologists and psychologists) will be blinded for fatty acid treatment regime. The duration of parenteral nutrition and the amount of fatty acids administered will be according to clinical routines.

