### **5.2 Inclusion Criteria**

Subjects must meet all the following inclusion criteria to be permitted into this study:

1. Signed informed consent from parents/guardians;
2. Subject must be born before 28 weeks of gestation

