### **Growth**

Length, weight and head circumference will be registered weekly from birth until 40 weeks postmenstrual age and at 2.0 y corrected age and at 5,5 y uncorrected age.

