- Postnatal growth development of weight, length, head circumference, at day 0, day 7, day 14, postnatal age (PNA) week 3-7, PMA week 30-40. For infants born at GA $\geq$ 24 weeks SDS will be calculated and summarized per treatment group. Otherwise, for all infants individual growth curves will be created separately by sex and GA week for the two treatment groups. No imputation of missing data is planned.

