### 3. Clarification on the analysis fatty acid secondary variable

**Original definition:** Postnatal serum fatty acid (in mol%) composition in preterm infants with and without AA:DHA supplementation (at 0h, 72h, day 7, day 14, every second week until PMA of 29 weeks and thereafter at 30, 32, 34, 36, 40 weeks PMA) will be analysed as secondary variable. Missing data will not be imputed, analysis will be performed using Mixed Models for Repeated Measures (MMRM) where missing data at random is assumed.

**Clarification:** Due to infants are born in different gestational weeks, serum fatty acid data for postnatal weeks 4 and 6 will be available only for a proportion of infants, those with the lowest gestational age at birth. Therefore postnatal weeks 4 and 6 will be only described but not used in planned MMRM analyses.

|                                     |                                    |               |  |
|-------------------------------------|------------------------------------|---------------|--|
| STATISTISKA KONSULTGRUPPEN          |                                    | Note-to-SAP 1 |  |
| Protocol:
Mega Donna Mega | Protocol No:
MEGADONNAMEGA 16-7 |               |  |
|                                     | Version:
1.0                    | Page 1 of 2   |  |

---

**SPONSOR:** [name]

**STUDY:** Mega Donna Mega

**TO:** SAP version 1.0 dated 19 November 2019

**DATE:** 14 April 2020

**SUBJECT:** Note-to-file to SAP - Clarifications

---

Following clarifications were not defined in detail in the final SAP and are documented in this note-to-file.

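### Note-to-SAP 1 limits the growth MMRM to birth and PMA weeks 30-40 without a reason, leaving the weekly measurements in between (18% to 44% of treatment time, by gestational age) out of the model

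*Combined protocol and SAP*

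**What the plan says.** **Growth.** Protocol 8.1 (Growth) states: "Length, weight and head circumference will be registered weekly from birth until 40 weeks postmenstrual age". Protocol 11.1 counts weight, length and head circumference among its important secondary endpoints. It plans a linear mixed model with subject as random factor and gestational age (GA) and treatment as fixed factors, and sets no limit on time points.

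SAP 3.2.2 lists growth "at day 0, day 7, day 14, postnatal age (PNA) week 3-7, PMA week 30-40". SAP v1.0 uses that list for standard deviation score (SDS) summaries and growth curves. SAP 4.6.2 adds SDS differences between groups with 95% CIs, and individual and mean curves by GA week and sex. It contains no growth MMRM.

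Note-to-SAP 1, item 3 (14 April 2020) replaces the list with: "Postnatal growth development of weight, length, head circumference, at day 0, and PMA week 30-40, will be analysed using mixed models". It gives no reason for the choice of time points. It keeps SDS summaries per group and does not mention the curves.

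**Fatty acids.** Samples are due "at 0h, 72h, day 7, day 14, every second week until PMA of 29 weeks and thereafter at 30, 32, 34, 36, 40 weeks PMA". Item 3 of the other set of SAP clarifications, which also redefines the safety and per-protocol populations, says that "serum fatty acid data for postnatal weeks 4 and 6 will be available only for a proportion of infants", and concludes: "Therefore postnatal weeks 4 and 6 will be only described but not used in planned MMRM analyses". The 72 h, day 7 and day 14 samples stay in the model. The model in SAP 4.6.2 has visit, treatment group and the level at birth, but no GA term. AA and DHA are second and third in the confirmatory sequence of SAP 4.1. Growth is not in that sequence, and SAP 4.6.2 treats it as descriptive.

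**The concern.** The supplement is meant to act from the start of life: "Enteral supplementation with AA:DHA will start at second enteral feeding after birth and continue once daily to postmenstrual week 40 + 0". The protocol's introduction stresses the large energy deficit and poor neonatal growth of extremely preterm infants, and its rationale says AA is thought to promote growth. The weeks just after birth are therefore of direct interest, and the measurements will exist.

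Under the note, the growth model sees birth and then nothing until PMA 30. An early benefit or harm that has reversed by then cannot show in it. An infant who dies or leaves before PMA 30 contributes nothing to the model after birth. The unmodelled stretch is longest for the most immature infants.

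The fatty acid clarification has a related weakness. It sets weeks 4 and 6 aside because only the lowest-GA infants have them. That availability is fixed by GA at birth, which is known for every infant. Once GA is in the model, such data can be used under the missing-at-random assumption that SAP 3.2.2 already makes. GA category is also a randomisation stratum. The primary analysis adjusts for it and the fatty acid model does not.

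**Working it through.** The documents give no figure for the share of treatment time left out of the growth model, so there is none to reproduce.

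**Inputs**
- Modelled growth times: day 0 and PMA 30-40 (Note-to-SAP 1, item 3).
- Treatment period: taken as birth to PMA 40+0 (protocol 4). The true start is the second feed, so this is off by about a day at most.
- Upper GA limit: "Subject must be born before 28 weeks of gestation" (protocol 5.2), so 27+6 is the highest eligible GA.
- Lower GA limit: none is stated. I assume 22+0, the lower end of the planning population in protocol 11.1.
- Lowest GA stratum: up to 24+6, with 84 of 210 planned infants = 40% (protocol 4).

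**Formulas, with GA in weeks**
- Growth: days from birth to PMA 30 = 7 × (30 − GA). Treatment days = 7 × (40 − GA). Share = (30 − GA)/(40 − GA).
- Fatty acids: gap from day 14 to PMA 30 = 7 × (30 − GA) − 14 days, divided by the same treatment days.
- Growth visits: those of day 7, day 14 and postnatal weeks 3-7 that fall before PMA 30, out of day 0 + those visits + 11 PMA visits.

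| GA at birth | Growth, no modelled value | Growth visits left out | Fatty acids, day 14 to PMA 30 |
|---|---|---|---|
| 22+0 | 56/126 days = 44% | 7/19 = 37% | 42/126 = 33% |
| 24+0 | 42/112 = 38% | 5/17 = 29% | 28/112 = 25% |
| 24+6 | 36/106 = 34% | 5/17 = 29% | 22/106 = 21% |
| 25+0 | 35/105 = 33% | 4/16 = 25% | 21/105 = 20% |
| 27+0 | 21/91 = 23% | 2/14 = 14% | 7/91 = 8% |
| 27+6 | 15/85 = 18% | 2/14 = 14% | 1/85 = 1% |

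In the lowest stratum the growth share therefore runs from 34% to 44%.

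**Who loses a fatty acid sample.** Week 4 falls at or before PMA 29+0 if GA + 4 ≤ 29, that is GA ≤ 25+0. Week 6 does so if GA + 6 ≤ 29, that is GA ≤ 23+0. If sampling runs through 29+6, the limits become 25+6 and 23+6. For more mature infants the gap in the last column comes from the sampling schedule, not from the clarification.

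**The case against.** **The case for the note.**
- For growth, the note adds a model and does not cut one back, because SAP v1.0 had no growth MMRM.
- PMA is a sensible common scale. Every surviving infant passes PMA 30 after birth, whereas the SAP list mixes two overlapping axes. At GA 27+6, postnatal weeks 3-7 fall at PMA 30+6 to 34+6, which the PMA visits already cover.
- Day 0 and PMA 30 bracket the early period, so net growth is captured.
- Growth is descriptive, and no confirmatory conclusion depends on it.
- The fatty acid exclusion has a stated reason and touches few samples.

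All of this is correct and keeps the point small. It does not supply the missing reason for the growth time points. Nor does it explain the departure from protocol 11.1, whose mixed model contained GA and had no such limit.

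**Stronger readings that the documents do not support.** A reader might infer that up to 44% of treatment time goes unanalysed for both growth and fatty acids. The 44% applies only to growth and only to a birth at 22+0. For fatty acids the gap is at most 33%, because samples through day 14 stay in the model. Unanalysed is also too strong: weeks 4 and 6 will be described, SDS summaries remain, and the curves in SAP 4.6.2 are not expressly withdrawn.

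Whether those analyses still cover the early weeks is unclear. The group differences in SAP 4.6.2 are tied to the time points studied, which the note redefines. The updated definition also omits the curve sentence that appears in the text it replaces.

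**Conclusion.** The point holds as a minor one. The growth MMRM leaves out every measurement between birth and PMA 30 without a stated reason, although the data are collected weekly. That interval is 18% of treatment time at GA 27+6, 34% at 24+6 and 44% at 22+0. The last figure rests on the assumed lower limit, and all three take treatment to run from birth to PMA 40+0.

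These are shares of time, not of statistical information. What the model loses is the path between birth and PMA 30, and with it any effect that comes and goes in that window. The documents give no evidence that such an effect is likely.

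For AA and DHA the consequence is formally closer to inference, because both are confirmatory. The change in the overall estimate is nevertheless expected to be small. That is a judgement, since the documents contain no data to test it. The clearer gap there is the missing GA term.

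**What to change.** **Growth (Note-to-SAP 1, item 3)**
- Include the day 7, day 14 and postnatal week 3-7 measurements in the MMRM, indexed by PMA week.
- Adjust for GA category and birth size. Day 0 then enters as a covariate and not also as a response.
- Report the treatment difference separately before PMA 30 and from PMA 30 on.
- Use unstandardised values where the SDS reference does not reach. SAP 3.1.1 applies the reference from 24 weeks, and the note extrapolates it at birth only. The day 7 value of an infant born at 22+0 falls at PMA 23+0.
- Confirm that the individual and mean curves in SAP 4.6.2 remain and cover the early weeks.
- If the early visits stay out of the model, state why.

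**Fatty acids (SAP 4.6.2 and the clarification)**
- Add GA category to the AA and DHA models.
- With it, keep weeks 4 and 6, at least as a sensitivity analysis. The limit for week 6 lies inside the lowest stratum, so GA in weeks would follow availability more closely than the category does.

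**Cost.** Note wording and some programming, with no new data. Cells at the earliest PMA weeks will be sparse and filled only by the most immature infants, so a structured covariance may be needed. Estimates at those weeks describe that subgroup only and should be labelled so.

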#### **Secondary endpoints**

Important secondary endpoints are:

- Body weight
- Length
- Head circumference

These will be modelled by a linear mixed effects model. Subject will be used as a random factor, and *GA* and *treatment* will be used as fixed factors.

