#### 4.6.2 Secondary Efficacy Analyses

Confirmatory analyses of secondary variables:

1. The secondary efficacy analyses of fatty acid levels over time will be evaluated by applying MMRM with the change in level of fatty acids (AA and DHA respectively) from birth as dependent variable, and visit, treatment group as fixed effects, fatty acid at birth as fix adjustment variable, with repeated measures by visit applying the covariance pattern (compound symmetry, autoregressive, Toeplitz, unstructured, overall and applied by treatment group) that minimizes the Akaike's Information Criterion (AIC). From this model without an interaction term the overall effect of the IP will be retrieved, presented by adjusted means with 95% CI. The assumption of normally distributed residuals will be checked by reviewing the diagnostic plots. If not satisfactory the sandwich estimators for the standard errors (resulting in wider CIs) will be applied. Additional model for descriptive (exploratory) purpose will be performed including interaction term from which the impact of IP over time will be retrieved and presented graphically.
2. The secondary efficacy analysis of the impact of IP on BPD will be analyzed on ITT population including infants for which BPD was evaluated at 36 weeks PMA, deaths and other drop-outs will be handled as non-events. Poisson regression with log-link function, will be performed, resulting in RRs with 95% CI and associated p-value.
3. The secondary efficacy analysis of the impact of IP on IVH (grade 0-4) will be analyzed on ITT population using all infants that have evaluated IVH, missing data will be considered as non-events. Mantel-Haenszel Chi-square test will be performed.

Following secondary variables will be analyzed descriptively:

1. PDA will be analyzed using Fisher's Exact test. Proportion of patients with events and 95% CI will be provided.
2. NEC will be analyzed in the same way as the primary efficacy variable, applying Poisson regression. RR with 95% CI will be provided.
3. Growth development, by computing difference with 95% CI between treatment groups in BWSDS, BLSDS, HCSDS for studied time points, only on infants born GA $\geq$ 24 weeks. Individual growth curves will be created by GA week and sex, per treatment group and mean curve estimated per each subgroup of infants.

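### Note-to-SAP item 3 lists size at birth among the growth measurements for the MMRM, gives it no baseline role and states no treatment contrast

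*Combined protocol and SAP*

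**What the plan says.** Note-to-SAP item 3 replaces the SAP's definition of the growth variable. Weight, length and head circumference "at day 0, and PMA week 30-40, will be analysed using mixed models for repeated measures (MMRM"), expressed as SDS, with the growth reference extrapolated at birth to infants born before 24 weeks. The item gives no fixed effects, covariance structure, birth covariate, baseline constraint or treatment contrast.

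Four other places bear on how it would be read:

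- Protocol 11.1, on the growth endpoints: "These will be modelled by a linear mixed effects model", with subject random and only GA and treatment fixed. That yields one overall treatment effect.
- SAP 4.6.2, on growth: "Growth development, by computing difference with 95% CI between treatment groups in BWSDS, BLSDS, HCSDS for studied time points". That is a set of differences by visit.
- SAP 4.6.2, on fatty acids, the only MMRM specified in full: the outcome is the "change in level of fatty acids (AA and DHA respectively) from birth as dependent variable", with "fatty acid at birth as fix adjustment variable". The treatment effect is a single one: "From this model without an interaction term the overall effect of the IP will be retrieved".
- Protocol section 4, on timing: "Enteral supplementation with AA:DHA will start at second enteral feeding after birth".

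**The concern.** The growth objective concerns growth after birth. Because the supplement starts after birth, the expected arm difference in birth size is zero whatever the supplement does. A birth value in the response vector therefore carries no information on the effect unless the model uses it as a baseline, and item 3 does not say that it does.

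A programmer has to fill the gap. If the single treatment effect of protocol 11.1 or of the fatty-acid MMRM is carried over, the quantity tested is a weighted mean difference over birth and PMA weeks 30-40. It is pulled towards zero, and a chance imbalance in birth size enters it directly. If differences are taken by visit, the birth value goes unused and the later comparisons are less precise than the data allow. The protocol ranks weight, length and head circumference as important secondary outcomes, and their intervals will be published.

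**Working it through.** **Plan's own figure.** There is none for growth. The only sample-size figure, 80 per group, concerns any ROP and does not bear on this point.

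**Inputs from the documents.** Day 0 plus weekly PMA 30 to 40 gives 1 + 11 = 12 measurements. Tests are two-sided at 0.05. The true difference at day 0 is zero.

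**Assumptions (the documents give no values).** 85 infants per arm (105 less 15% deaths is 89, less a few more losses); SDS with unit SD; a constant true difference of 0.4 SD at PMA 30-40; birth-to-later correlation 0.5; correlation between adjacent later weeks 0.90, 0.95 or 0.97, falling autoregressively with distance.

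**Reading 1: one overall treatment effect.** With covariance V of the 12 values, the generalised least squares weights are w = V⁻¹1 / (1′V⁻¹1). The expected estimate is 0.4 × (1 − w₀), where w₀ is the weight of day 0. The SE is √[(2/85) / (1′V⁻¹1)], and power is Φ(estimate/SE − 1.96). With birth as covariate, V is replaced by the later-visit covariance less 0.5² in every cell, and the estimate stays at 0.4.

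*Weights from V (unstructured covariance fitted):*

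| Adjacent-week correlation | 0.90 | 0.95 | 0.97 |
|---|---|---|---|
| Weight of day 0 | 24% | 37% | 42% |
| Expected estimate (SD) | 0.31 | 0.25 | 0.23 |
| Power, day 0 in response | 72% | 51% | 43% |
| Power, later visits only, no covariate | 90% | 83% | 80% |
| Power, later visits, birth covariate | 98% | 94% | 91% |

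Example at 0.95: 0.4 × (1 − 0.372) = 0.251; SE 0.127; ratio 1.98; power 51%. Day 0 takes so much weight because the later weeks are so alike that together they act almost as one observation.

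*Equal visit weights (a random subject intercept, i.e. compound symmetry):* day 0 weighs 1/12 = 8%, and the estimate is 0.4 × 11/12 = 0.37.

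| Adjacent-week correlation | 0.90 | 0.95 | 0.97 |
|---|---|---|---|
| Power, day 0 in response | 83% | 77% | 74% |
| Power, later visits only, no covariate | 87% | 81% | 79% |
| Power, later visits, birth covariate | 97% | 93% | 90% |

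Here day 0 in the response costs about 4-5 points, and the missing birth covariate a further 10-11.

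**Reading 2: differences by visit.** Unadjusted at week 40: SE = √(2/85) = 0.153; 0.4/0.153 = 2.61; power 74%. Adjusting for birth multiplies the SE by √(1 − ρ²), where ρ is the correlation with birth size:

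| ρ | SE | 0.4/SE | Power |
|---|---|---|---|
| none (unadjusted) | 0.153 | 2.61 | 74% |
| 0.3 | 0.146 | 2.73 | 78% |
| 0.5 | 0.133 | 3.01 | 85% |
| 0.7 | 0.110 | 3.65 | 95% |

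Day 0 has no effect on these contrasts. The whole gain comes from using birth size as a covariate.

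**The case against.** A reader might infer that the growth test, as planned, partly compares the arms before treatment and so loses much of its power. The documents do not support that as a statement of fact, for these reasons:

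- Item 3 defines no treatment test. SAP 4.6.2 reports growth differences by time point, and the note does not withdraw that line. Under that reading nothing is diluted.
- Listing a baseline time need not make it a response. SAP 3.2.2 lists 0h for the fatty acids in the same way, yet the model in SAP 4.6.2 uses the birth value as baseline. Item 3 amends the same kind of variable definition.
- The largest losses join two sources. The single effect comes from protocol 11.1 or the fatty-acid model. Protocol 11.1 has a random subject factor, which implies equal weights and 8% for day 0. Unstructured covariance is only one of the fatty-acid candidates ("compound symmetry, autoregressive, Toeplitz, unstructured"), and none is named for growth.
- The correlations and effect pattern are assumed. With purely autoregressive covariance over all visits and an effect that grows with time, a separate calculation scaled to an 80% reference gave the overall test 88-93%, so there was no loss.
- Growth is outside the five confirmatory tests in SAP 4.1, and its p-values are descriptive. Birth SDS by arm is tabulated, so an imbalance would be seen.

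All of this stands, and it limits the point. It does not remove it: for fatty acids SAP 4.6.2 states the baseline role, whereas for growth no document does. Under either reading, birth size, already collected, is not used for adjustment.

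**Conclusion.** The point holds as a gap in item 3 with a concrete cost in precision. It is conditional on how the model is read:

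- **One overall effect:** the estimate is diluted by 8% under compound symmetry, and by 24-42% under unstructured covariance with the assumed correlations.
- **By-visit differences:** there is no dilution, but week-40 power is 74% where birth adjustment would give about 78-95%.

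The power figures rest on 85 per arm, a 0.4 SD difference and the stated correlations, none of which the documents supply for growth. Because growth is analysed descriptively, severity is limited. This is a worthwhile and nearly free improvement, and no confirmatory result is shown to be wrong.

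**What to change.** Amend Note-to-SAP item 3 to say:

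- The response is SDS at PMA weeks 30-40, with treatment, visit and treatment-by-visit as fixed effects and the birth SDS of the same measure as covariate. Alternatively, keep day 0 in the response with the arm means constrained equal at birth.
- The contrast reported is named, for example the adjusted difference at PMA week 40 or averaged over PMA 30-40, with its 95% CI.
- Day 0 by arm appears in the baseline table.

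This brings growth into line with the baseline adjustment that the SAP already makes for fatty acids. The cost is a sentence or two in the note and a changed model statement; no new data are needed. The covariate version drops infants who lack a birth measurement, and the constrained version keeps them.
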